## Methods and design

### Design

This will be a multi-centre, prospective, single blinded, block randomised controlled trial. Participants will be stratified according to mobility level using the mobility section of the Guys Neurological Disability Scale[24]. Those who score 0, 1 or 2 are stratified to stand A, those scoring 3 and 4 to strand B. For each strand blocks of subjects will be randomised to one of the interventions or to the control group.

Strand A will concern individuals with MS who walk independently or use one stick to walk outside. The objective is to compare the immediate and long term effect of yoga, physiotherapy led exercise class, fitness instructor led exercise class to a control group who don't change their exercise habits.

Strand B will concern individuals with MS who walk with bilateral support or a rollator, they may use a wheelchair for longer distance outdoors. The objective is to compare the immediate and long term effect of 1:1 Physiotherapist led intervention, group intervention led by Physiotherapist, or group yoga intervention to a control group who don't change their exercise habits.

The study protocol was approved by 10 regional ethics committees in the Republic of Ireland

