### Assessment

Each participant will be assessed by a blinded assessor who is unaware of group allocation. Assessors will attend training days in order to standardise the measurements.

Assessments will be carried out at baseline (week 1), post-intervention (week 12) and at follow-up (week 24). The following outcome measures will be used for all three assessments: Multiple Sclerosis Impact Scale 29 version 2 (MSIS), Modified Fatigue Impact Scale (MFIS), six minute walk test (6MWT), physiological cost index (PCI), and hand held dynamometry (HHD). In addition the Berg Balance Scale (BBS) and the Modified Ashworth Scale (MAS) will be used for strand B. As equipment for PCI and HHD are not available to all assessors some participants will not have these measures recorded. The more physically demanding outcome measures were separated to avoid fatigue and so the order of testing for strand A was 6MWT including PCI, MSIS, HHD, MFIS. For strand B it was 6MWT including PCI, MSIS, BBS, MFIS, MAS, HHD

A standardised assessment at baseline considered the participants suitability for exercise and measured confounding variables such as level of sensory loss, coordination deficits etc.

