### Statistical Analyses

All measures will be summarised and tested for normality. If variables are non-normal then Wilcoxon Signed Rank tests will be used to test for differences before and after interventions and Mann-Whitney U tests will be used to test for differences between groups before and after interventions. If the variables are reasonably normally distributed then repeated measures ANOVA will be carried out to test for differences between groups and over time. Suitable plots will be used to demonstrate the changes found.

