## Discussion

This multi-centre, prospective, single blinded, block randomised controlled trial aims to determine which physiotherapy or exercise intervention MS Ireland should deliver in order to reduce the impact of MS, reduce fatigue and optimise activity in people with MS. It uses the recommendations of the Cochrane review[6] by including blinded assessments, concealing allocation to groups and documenting drop outs in detail. If sufficient numbers are recruited sub-group analysis may be carried out in order to analyse which impairments are associated with success from each of the interventions, or who does best from what treatment.

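### For outcomes judged normal, a classical three-visit repeated measures ANOVA would discard the observed week 12 result of anyone who misses week 24

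*Protocol article*

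**What the plan says.** The Statistical Analyses section of the protocol article makes the method depend on a check of normality.

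- Reasonably normal: "repeated measures ANOVA will be carried out to test for differences between groups and over time".
- Non-normal, within group: "Wilcoxon Signed Rank tests will be used to test for differences before and after interventions".
- Non-normal, between groups: "Mann-Whitney U tests will be used to test for differences between groups before and after interventions".

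The Assessment section sets visits at weeks 1, 12 and 24 and introduces the list of measures with "The following outcome measures will be used for all three assessments". The Design section gives both strands an immediate and a long-term aim; for Strand A it begins "The objective is to compare the immediate and long term effect of yoga". The Discussion says that the trial follows a Cochrane review's advice, including "concealing allocation to groups and documenting drop outs in detail".

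The Interventions section says that controls have no intervention for 12 weeks and are then offered a treatment of their choice, and that their response to it is not assessed within the trial. No drop-out rate is given, and the Statistical Analyses section does not say which visits enter the ANOVA.

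**The concern.** With three scheduled visits and aims at both time horizons, the natural reading of the ANOVA sentence is a group-by-time analysis over weeks 1, 12 and 24. In its classical form that analysis needs all three values from each person. Someone with a baseline and a week 12 value who does not return at week 24 is removed altogether, including from the comparison at the end of the intervention, although the data for that comparison were collected.

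Two things are at stake. One is precision: observed week 12 results are thrown away. The other is bias: the week 12 effect is estimated only in people who came back 12 weeks later. If returning depends on how they had done by week 12, and depends on it differently across arms, the comparison between groups is distorted. The trial is meant to tell MS Ireland which intervention to deliver, so that distortion bears directly on its purpose.

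The complaint is not that a missing-data section is absent. A condensed article may leave that to the full protocol or analysis plan. The article does name a method, and in its usual form that method discards data.

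**Working it through.** **1. Who is kept by each method.** Take 60 people, of whom 12 miss week 24 only.

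- Signed rank, week 1 against week 12: 60 pairs kept.
- Signed rank, week 1 against week 24: 60 − 12 = 48 pairs kept.
- Classical repeated measures ANOVA over three visits: 48 people kept, so 12 observed week 12 results are lost. One standard routine simply refuses the unbalanced data.

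A Mann-Whitney test at week 12 likewise needs only the visit, or the change, being tested. The loss is therefore specific to the ANOVA.

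**2. The plan's own sample sizes.** The inputs are in the Sample size calculations section: 60 per group with probability 0.329 (Strand A), 22 per group with probability 0.217 (Strand B), significance level 0.05, power 90%. Noether's two-group Mann-Whitney formula, two-sided, is

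n per group = (1.960 + 1.282)² / [6(p − 0.5)²]

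- Strand A: 10.51 / (6 × 0.171²) = 59.9, rounded up to 60.
- Strand B: 10.51 / (6 × 0.283²) = 21.9, rounded up to 22.

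Both figures are reproduced, with no allowance for drop-out. The article attributes them to the signed rank test, whose formula has 3 in place of 6 and gives 120 and 44. That mismatch is a separate matter. It is mentioned here only to explain why the Mann-Whitney formula is the yardstick below.

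**3. Effect of losing week 12 values.** Assumption, since the article gives no rate: 10%, 20% or 30% are missing at week 24, and half of those are already missing at week 12. Power = Φ(√(6n) × |p − 0.5| − 1.960).

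| Missing at week 24 (week 12) | Strand A n, all available / three-visit complete | Power | Strand B n, all available / three-visit complete | Power |
|---|---|---|---|---|
| 10% (5%) | 57 / 54 | 88.5% / 86.8% | 20.9 / 19.8 | 88.7% / 87.0% |
| 20% (10%) | 54 / 48 | 86.8% / 82.7% | 19.8 / 17.6 | 87.0% / 82.8% |
| 30% (15%) | 51 / 42 | 84.9% / 77.5% | 18.7 / 15.4 | 85.0% / 77.6% |

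Worked case, Strand A at 20%:

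- All available: √(6 × 54) × 0.171 − 1.960 = 1.118, power 86.8%.
- Three-visit complete: √(6 × 48) × 0.171 − 1.960 = 0.942, power 82.7%.

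These are Mann-Whitney powers at the planning effect, used to show the cost of the smaller n. They are not powers of the ANOVA, for which the article gives no standard deviation.

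**4. Bias.** A simulation (4,000 trials) used two groups of 60, no true effect, correlation 0.6 between visits and about 20% missing week 24. In one arm the chance of missing week 24 rose with a worse week 12 change; in the other it was a constant 20%. The mean group difference in week 12 change was 0.00 SD with all available data and −0.14 SD after deleting those without week 24. Low MSIS scores are good, so the spurious difference favours the arm that loses its poor responders.

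**The case against.** Several parts of the opposing case stand.

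- **The branch is conditional.** The ANOVA applies only to outcomes judged reasonably normal, and the sample size section treats parametric tests as the alternative. A reader might infer that the before-after and Mann-Whitney tests also lose week 12 results when week 24 is missed. They do not; they omit only people missing a visit that is being tested.
- **Three visits are inferred.** If the ANOVA used weeks 1 and 12 only, or were fitted as a mixed model, nothing would be lost. The text on controls' later treatment lends some support to a comparison with control that ends at week 12. The three scheduled assessments and the long-term aim point the other way. The article does not settle it.
- **Stopping class is not missing an assessment.** A reader might infer that people who leave a class drop out of the analysis. The Assessment section says that each participant is assessed and sets no attendance condition, and attendance is recorded separately.
- **Retention wording, drop-out reporting by arm and sensitivity analyses** may sit in the full protocol or analysis plan. Their absence from an article is not a fault.
- **Size in MSIS points.** A reader might want the bias stated as a percentage overstatement of the Strand A pilot change of 8.8 points (62.4 − 53.6). That would need an assumed standard deviation, correlation, loss and strength of dependence, none of which the article gives. It would also describe a change within one arm, not the difference between arms.

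What remains is that a named method, on its most natural reading, discards collected primary-outcome data, and a better method is available at almost no cost.

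**Conclusion.** The point holds for the ANOVA branch, on the condition that the ANOVA is fitted classically over weeks 1, 12 and 24. The week 12 comparison is then one of people with all three visits. At an assumed 20% missing week 24, Strand A loses 6 observed week 12 values per group (54 − 48) and about 4 percentage points of power; across assumed losses of 10% to 30% the power cost is about 2 to 7 points, and Strand B is similar. That loss is modest. Bias may matter more, but it arises only if missingness depends on the week 12 change and differs by arm; the −0.14 SD illustrates the mechanism and does not predict this trial. This is a worthwhile, cheap improvement to a stated method, not an error that undermines the trial.

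**What to change.** Replace the repeated measures ANOVA with a likelihood-based mixed model for repeated measures that:

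- uses every available visit, so that a missing week 24 does not remove a week 12 value;
- analyses everyone in the group to which they were allocated;
- estimates week 12 and week 24 separately.

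Name the week 12 contrast as the comparison with control. The Interventions section offers controls a treatment of their choice after the control period and says that the response is not assessed, while the Assessment section schedules week 24 for every participant. The two passages must be reconciled, so that it is clear whether controls have a week 24 value and what it represents.

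The model is valid if missingness depends only on observed values, which is weaker than what the completers' analysis needs. The rank tests can stay as written on this point. Separately, whole blocks of 8 people are allocated together; neither the power figures above nor the change proposed here deals with that.

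The cost is a change of wording and a little more analysis work, with no new visits or participants. The estimate may prove less favourable than the completers' figure.

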## Discussion

This multi-centre, prospective, single blinded, block randomised controlled trial aims to determine which physiotherapy or exercise intervention MS Ireland should deliver in order to reduce the impact of MS, reduce fatigue and optimise activity in people with MS. It uses the recommendations of the Cochrane review[6] by including blinded assessments, concealing allocation to groups and documenting drop outs in detail. If sufficient numbers are recruited sub-group analysis may be carried out in order to analyse which impairments are associated with success from each of the interventions, or who does best from what treatment.
